## Methods

### Study design and setting

The present study is a multicenter, double-blind, randomized controlled trial (RCT) with six conditions. The interventions consist of two alcohol-specific inhibition trainings (with different Go/NoGo ratios) and one control inhibition training that is not context specific. In each version of the training, six sessions will be performed over the space of 2 weeks. Next to the three versions of the training, different samples will perform the training in different times of the day (morning/afternoon), resulting in a total of six conditions. Between the three study sites, 246 abstinent inpatients with AUD will be recruited. To compare our patient sample to the healthy population, we will measure 30 (behavioral) and 20 (EEG) healthy participants at one point in time. The duration of the study from the first inclusion to the last participant’s follow-up is 36–40 months. Recruitment, randomization, and baseline measurements (T1) will take place at one of the three study sites at the beginning of the regular inpatient program. All patients will have undergone detoxification prior to entering this inpatient program. Pre-training assessment (T2) is usually performed by the end of the second week or at the beginning of the third week of the inpatient stay and is followed by the 2 weeks, during which the six training sessions of the intervention or the control training are performed. Post-training assessment (T3) takes place 1 to 4 days after the last training session. At discharge (T4), the last measurement during inpatient program is performed. The duration of the inpatient stay typically varies between 8 and 12 weeks, depending on individual and institutional factors. Follow-up assessments take place 3 (T5), 6 (T6) and 12 (T7) months after discharge and consist of a questionnaire battery and a telephone interview (see also “Procedure” and Fig. 1).

**Fig. 1 Fig1:**
[figure not shown]
Study design of the INTRA study. Note that for the cortisol substudy, salvia-cortisol samples will be collected before and after the first training session. *Alc-IT* alcohol-inhibition training, *EEG* electroencephalography, GNG *Go-NoGo Task*, *IAT* Implicit Association Test, *INTRA* Abbreviation of the study name: INhibition TRaining in Alcohol use disorder, *n* sample size, *SST* Stop-Signal Task, *TLFB* Timeline-follow-back, *Q* questionnaire

### Participants

#### Patients

We will screen all patients who previously completed a detoxification and then entered an alcohol-specific inpatient treatment program at one of three specialized addiction treatment centers in Switzerland, namely the Suedhang Hospital (Bern); the Forel Hospital (Zuerich) and the Psychiatric Hospital of Muensingen (Bern). Inclusion criteria are age 18–60 years and abstinence from alcohol for at least 4 weeks prior to the first training session. Exclusion criteria are other main psychiatric diagnoses than AUD (comorbidities are allowed as long as AUD is considered to be the main diagnosis), other severe SUD (except nicotine; Drug Use Identification Test (DUDIT [47, 48]) ≥ 25 per substance), no diagnosed neurocognitive problems (e.g., Korsakoff syndrome) in the medical history, current medical conditions preventing participation (e.g., acute infectious diseases), the inability to read and understand the participant’s information and the enrollment of an investigator, their family members, employees and other dependent persons. Written informed consent will be obtained from all patients at the beginning of the study.

#### Healthy controls

In order to compare behavioral data of the patient sample to that of a healthy population, 50 healthy controls will be measured at one point of time (20 with EEG). Inclusion criteria for healthy controls are age 18–60 years, non-problematic drinking behavior (Alcohol Use Disorders Identification Test (AUDIT [49]) < 8; Alcohol Use Disorder Scale (AUD-S [50]) < 2)), and no signs of psychopathology (Brief Symptom Check List (BSCL [51, 52],) GSI_t-value_ ≤ 63). Exclusion criteria consist of current treatment for a psychiatric diagnosis and/or psychopharmacological medication, treatment for SUD in the past, problematic substance use (except nicotine; DUDIT ≥8 per substance, e.g., cannabis), neurocognitive problems, poor health conditions, the inability to read and understand the study information. In the substudy EEG, additional exclusion criteria are the occurrence of AUD in first-degree relatives and hearing impairments. Written informed consent will be obtained from all healthy controls prior to inclusion. For a tabular overview of all in- and exclusion criteria, see Additional file 1.

### Stimulus material

#### Stimuli for training, GNG and IAT

A total of 40 pictures of alcoholic beverages, water and neutral objects were created by the study team. All pictures were photographed with a high-resolution camera (Nikon D810, Nikon Inc., Tokyo, Japan) in a neutral setting with a white background and the same light conditions (two spotlights). Water pictures are the same for all participants, whereas alcohol pictures will be matched to the individual’s drink of choice. For this purpose, three sets with either beer (seven lager, one wheat), wine (two red, two white, two rosé, two sparkling wines) or spirits (two vodka, two whiskey, two liquor, one gin, one tequila) were generated. Each of the four beverage sets includes eight pictures of brands commonly consumed in Switzerland, with all pictures comprising a bottle or can and a full beverage-specific glass (for examples, see Additional file 2).

The eight neutral stimuli are everyday objects (e.g., a flashlight plus battery) and were selected by complexity, shape and familiarity. All pictures were edited with GIMP software (GIMP 2.8.18, retrieved from https://www.gimp.org) and adjusted for size, centralization, brightness and background to ensure picture similarity.

#### Stimuli for SST

For the third task, stimulus material consist of 16 pictures (344 × 400 pixel) of a database and are characterized by their alcohol relatedness, valence, craving, arousal, luminance, colors and visual complexity [53]. Four pictures of each drink of choice (beer, wine and spirits), shot in (social) daily situations within a building, and four pictures of everyday objects (e.g., a hydrant) located outdoors, were selected. This additional stimulus material was chosen to test for generalization of the effect of our intervention to a novel inhibition task and to new stimuli.

### Intervention

Participants in both versions of the Alc-inhibition training (Alc-IT) are, as the name suggests, trained in alcohol-specific inhibition: pictures of alcoholic beverages will be consistently paired with a NoGo cue, while Go cues will be distributed among the other picture types (water, neutral). In contrast, for patients in the control training group, all three picture types will be paired equally often with NoGo cues and Go cues (see Table 1).*Alc-IT (50/50)*: the first training group will operate with a Go/NoGo ratio of 50/50, as implemented in prior studies [32, 33]: This original version of the Alc-IT will include 80 alcoholic NoGo trials as well as 80 non-alcoholic Go trials. In order to match both Alc-IT versions in training length while keeping the number of Alc-NoGo pairings constant, an additional 80 neutral Go trials and 80 neutral NoGo trials were included*Alc-IT (75/25)*: the second version of the Alc-IT will operate with a Go/NoGo ratio of 75/25. It will equally include 80 alcoholic NoGo trials and 80 non-alcoholic Go trials, but contrary to Alc-IT (50/50) 160 neutral Go trials will complete the set. Both Alc-IT versions thus include the same number of Alc-NoGo pairings and are of the same length, but differ in their Go/NoGo ratio and thus in the difficulty regarding inhibition control*Control training*: the control group will receive a training that consists of 80 non-alcoholic, 80 alcoholic, and 160 neutral trials. This control training is thus a non-specific inhibition training which is of equal length to other two groups and includes the same number of alcohol-related pictures in it, but all pictures will appear with equal probabilities as Go or NoGo trials while the Go/NoGo ratio is kept at 50/50

**Table 1 Tab1:** Distribution of trial types in the three training versions

	Alc-IT (50/50)		Alc-IT (75/25)		Control training	
	Trial type		Trial type		Trial type	
Picture types	Go	NoGo	Go	NoGo	Go	NoGo
Alcohol	–	80	–	80	40	40
Water	80	–	80	–	40	40
Neutral	80	80	160	–	80	80
Total trials	320		320		320	

All three versions of the inhibition training were programmed with Inquisit 5 (Version 5.0.5.0., Millisecond Software, Inc., Seattle, WA, USA). They are based on the script by Houben, Havermans [32], Houben, Nederkoorn [33], which was gratefully received by the authors and adapted to their own version. Go and NoGo cues are represented by the letter “p” or “f” next to one of the four corners of the alcohol, water or neutral pictures (1047 × 1080 pixel), whereby the assignment to the letters will be counterbalanced across participants. Participants will be instructed to press the space bar when a Go cue has been displayed and to refrain from pressing it when a NoGo cue has appeared. Each version of the training lasts approximately 13 min and consists of 320 trials, which are presented in a randomized order. A trial includes the simultaneous presentation of a picture and a cue (paired in accordance with the intervention version) and is visible on screen for 1500 ms. Participants are instructed to respond as fast as possible, unless the picture is paired with a NoGo cue. 500 ms after the (non)response visual feedback will be given, with a green circle indicating a correct (non)response, and a red cross indicating an incorrect (non)response. Based on data by Eberl et al. [54], which compared learning outcome after varying numbers of sessions of computerized training in AUD patients, participants will perform six training sessions.

### Interviews and questionnaires

#### Demographics

Relevant demographics (e.g., age, gender, education) as well as relevant information about past AUD treatment or other mental health problems will be assessed.

#### Diagnostics

The German version of the semi-structured interview of the *Diagnostic Expert System for Psychiatric Disorders* (DIA-X, adapted to the *Diagnostic and Statistical Manual of Mental Disorders* (DSM-5); [55])) specifically for AUD will be performed by a trained member of the study team. The original DSM-IV version was modified to meet the DSM-5 criteria, whereby the symptom craving was added and the question about legal issues was removed.

#### Alcohol use disorder and other substance use

The screening questionnaire *Alcohol Use Disorders Identification Tests* (AUDIT; [49]) from the World Health Organization (WHO) consists of 10 items on recent alcohol use, AUD symptoms, and alcohol-related problems.

With the *Alcohol Use Disorder - Scale* (AUD-S; [50]; adapted to DSM-5), self-rated AUD symptoms are measured, whereas this adapted version additionally includes craving as a criteria.

To assess patients’ alcohol use in the last 90 days prior to their current detoxification, an adapted version of the *Health and Daily Living Form* (HDL; [56]) will be used, which was also employed in a large, Swiss multicenter study [57, 58]. Patients will be asked about their consumption frequency and quantity of beer, wine, liquor and spirits, resulting in total number of standard drinks (SD; 1 SD equates to 3 dl beer, 1 dl wine, 2 cl spirits/liquor, or 10 g of pure alcohol) consumed per day. Separate items assess the PDA and the number of HDD for the last 90 days.

To measure the drinking behavior for each of the past 90 days, the *Timeline Follow-back* (TLFB; [59, 60]) method will be performed, which will be administered by an interview (face-to-face at T1 or telephone at T5) with a trained member of the study team. As in the HDL, the amount of alcohol per day will be assessed in standard drinks per day, but in contrast is conducted through a guided, standardized interview. The TLFB provides a report of drinking pattern, including PDA, HDD and TFD.

With the *Drug Use Identification Test* (DUDIT; [47, 48]), participants will be screened for substances (except nicotine) other than alcohol. Patients with other severe substance use and healthy controls with a problematic substance use are not eligible for this trial (see also “Inclusion/exclusion” criteria).

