#### Main study

Training effects on our primary outcome measures (PDA and HDD at 3-month follow-up) will be assessed with a 2 × 3 analysis of variance (ANOVA) with the factors time point (T1, T5) and training group (Alc-IT (50/50), Alc-IT (75/25) or control). Further, a Cox regression will be computed to predict the effect of the intervention on TFD (at 3-month follow-up).

Training effects on experimental test parameters will be assessed with a 2 × 2 × 3 repeated measures ANOVA with the factors measurement point (T2, T3), time of day (morning, afternoon) and training group (Alc-IT (50/50), Alc-IT (75/25) or control). Where Mauchly’s test of sphericity indicates heterogeneity of covariance, we will verify repeated measures results with Greenhouse-Geisser corrections.

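### The standard-drink rule equates 2 cl of spirits with 10 g of alcohol, but 2 cl at about 40% holds about 6.3 g, so spirits intake is overstated and some heavy-drinking days may be misclassified

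*Protocol article*

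**What the plan says.** The unit is set in the protocol article, under *Alcohol use disorder and other substance use*: "1 SD equates to 3 dl beer, 1 dl wine, 2 cl spirits/liquor, or 10 g of pure alcohol". For the Health and Daily Living Form (HDL), "Patients will be asked about their consumption frequency and quantity of beer, wine, liquor and spirits", and the answers are turned into standard drinks per day. The TLFB uses the same unit: "As in the HDL, the amount of alcohol per day will be assessed in standard drinks per day".

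HDD appears in both instruments. For the HDL, "Separate items assess the PDA and the number of HDD for the last 90 days". For the interview, "The TLFB provides a report of drinking pattern, including PDA, HDD and TFD". The section places the TLFB at T1 and T5, the two time points of the primary analysis described under *Main study*: "Training effects on our primary outcome measures (PDA and HDD at 3-month follow-up) will be assessed with a 2 × 3 analysis of variance".

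The section *Stimuli for training, GNG and IAT* shows which products the trial counts as spirits: "two vodka, two whiskey, two liquor, one gin, one tequila". The article gives no beverage strengths, no threshold for a heavy-drinking day, and no statement of which instrument supplies the HDD that is analysed.

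**The concern.** The definition presents three volumes and one mass as interchangeable. This is a stated scoring rule, not a detail left to another document, and its spirits term does not agree with its gram term at any ordinary strength. The rule also gives spirits and liquor one shared volume, although the HDL asks about them separately. If they differ in strength, 2 cl cannot hold 10 g for both.

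The unit feeds the daily amounts in the TLFB, the only instrument described as giving both a daily record and HDD. If HDD is obtained by counting those units against a cut-off, a spirits day reaches the cut-off with less ethanol than a beer or wine day. A patient who changes beverage between T1 and T5 could then change HDD status at constant ethanol intake. Any statement that these units are 10 g each would also be wrong for spirits.

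**Working it through.** **Inputs.** From the article: 3 dl beer, 1 dl wine and 2 cl spirits/liquor, each set equal to 10 g. Assumed, because the documents do not give them: ethanol density 0.789 g/ml, and strengths by volume of 4–5% (beer), 12–13% (wine), 35–50% with 40% as central value (spirits).

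**Formula.** Grams = volume in ml × strength × 0.789.

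**Reproducing the stated 10 g.**

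| Term | Strength needed for 10 g | Grams at assumed strengths | Reproduced? |
|---|---|---|---|
| Beer, 300 ml | 10 / (300 × 0.789) = 4.2% | 9.5 g at 4%, 11.8 g at 5% | approximately |
| Wine, 100 ml | 10 / (100 × 0.789) = 12.7% | 9.5 g at 12%, 10.3 g at 13% | approximately |
| Spirits, 20 ml | 10 / (20 × 0.789) = 63.4% | 5.5 g at 35%, 6.3 g at 40%, 7.9 g at 50% | no |

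With density 0.8, the spirits term still needs 62.5%. A weaker liquor is further off: 3.2 g at 20% and 4.7 g at 30%.

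**Overstatement for spirits.** 10 / 6.31 = 1.58 at 40%; 10 / 7.89 = 1.27 at 50%; 10 / 5.52 = 1.81 at 35%. Conversely, 10 g at 40% is 10 / (0.40 × 0.789) = 31.7 ml, about 3.2 cl, and 2 cl is 6.3 / 10 = 0.63 of a 10 g drink.

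**Effect on HDD if it is counted from TLFB units.** Take a cut-off of k drinks, meant as 10k grams, and a day on spirits only. The 2 cl rule calls the day heavy from 2k cl. At 40%, 10k grams is reached at 10k / (0.40 × 0.789) ml. Days between the two volumes are wrongly classed as heavy.

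| Assumed cut-off | Heavy under 2 cl rule from | Grams there (40%) | Gram cut-off reached at | Misclassified band |
|---|---|---|---|---|
| 4 drinks | 8 cl | 25.2 g | 12.7 cl | 8 to <12.7 cl |
| 5 drinks | 10 cl | 31.6 g | 15.8 cl | 10 to <15.8 cl |
| 6 drinks | 12 cl | 37.9 g | 19.0 cl | 12 to <19.0 cl |

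For 5 drinks, the upper end is 12.7 cl at 50% and 18.1 cl at 35%. Days below or above the band are classified the same way under either conversion.

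**Change of beverage.** Inside the band, 12 cl of spirits at 40% is 37.9 g and scores 6 drinks. The same ethanol as 12.5% wine (9.86 g per dl) scores 37.9 / 9.86 = 3.8 drinks, so the day crosses a 5-drink cut-off. Outside the band, 20 cl is 63.1 g and scores 10 drinks; as wine it scores 63.1 / 9.86 = 6.4. Both are heavy at cut-offs of 4 to 6, so HDD does not change.

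**The case against.** The strongest reply concerns the consequence, not the arithmetic. A reader might infer that HDD is overcounted. The article does not establish that: it states no threshold, the HDL takes HDD from a separate item, and the source of the analysed HDD is not fixed. Misclassification requires that HDD be counted from TLFB units, that spirits be entered by the 2 cl rule, and that the day's intake fall inside the band. This objection stands.

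A reader might also infer a biased treatment comparison. One rule applies to all randomised groups, and the TLFB is used at both T1 and T5, so the documents support misclassification common to the arms and nothing more. Nor does the existence of a spirits picture set show how many patients drink spirits.

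It is tempting to say that a spirits drinker is classed as heavy at about half the ethanol of a beer drinker. That ratio depends on choosing 5% beer. Where 3 dl of beer holds exactly 10 g, the ratio is about 1.6.

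Finally, the adapted HDL was also used in a large Swiss multicenter study, and keeping its unit may help comparability. That is a reason to report results under the 2 cl rule as well. It does not make 2 cl equal to 10 g.

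**Conclusion.** The stated equivalence is wrong for spirits, and this holds for any strength below about 63%. At 40%, one spirits unit is about 6.3 g, and standard drinks per day are overstated for spirits by a factor of about 1.6 (1.3 to 1.8 over 50 to 35%). The effect on HDD is conditional and limited to a band of spirits days: 10 to under 15.8 cl at 40% and an assumed cut-off of 5 drinks. Its frequency in this sample cannot be judged from the documents.

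PDA and TFD depend on whether any alcohol was drunk, not on how much, so the conversion does not touch them. The sample size of 244 was computed from an effect size of f = 0.2, α = 0.05 and power 0.8, and does not use the conversion. The strengths, the density and the cut-offs are assumptions.

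**What to change.** Reconcile the volume and gram definitions with one fixed gram conversion per beverage class, and divide by 10 g to obtain standard drinks. At an assumed 40%, 2 cl of spirits counts as about 0.63 of a standard drink. Give liquor its own conversion if its strength differs. Apply the same conversion to TLFB data at T1 and at follow-up, wherever beverage type and volume are recorded, and report HDD under the 2 cl rule as a sensitivity analysis.

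Where only unit counts were stored, keep the scoring as it is and do not describe those units as 10 g for spirits. Do not rescore T5 from the HDL: the article describes that form only for the 90 days before the current detoxification, and it asks for frequency and quantity, not a record of each day.

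The cost is a short conversion table and some rescoring. Interviewers must record beverage and volume instead of a unit count. The article reports that data collection is under way, and stored unit counts cannot be fully rescored.

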#### Alcohol-related constructs

Alcohol craving will be measured by the *Obsessive Compulsive Drinking Scale,* (OCDS-G; [61]). The items of the OCDS-G are divided into two subscales: control and consequences, and drinking obsessions.

As a second measure for craving, three specific questions will be asked [57, 58], which are scored from 0 (non-existent or never) to 10 (very strongly or always): “How strong was your urge to drink alcohol (on average) during the past 7 days?”; “Think of the moment during the past 7 days, in which the urge to consume alcohol was the highest. How strong was the urge?”; and “How often did you have the urge to drink alcohol during the past 7 days?”

Motivation to change alcohol use will be assessed with the *Stages of Change Readiness and Treatment Eagerness Scale* (SOCRATES; [62]), whereby only the subscale *Taking Steps* will be used. It indexes whether the person has already taken action to positively change their drinking behavior.

A second measure for motivation consists of three items on an 11-point Likert scale, summed up as *Motivation* [41, 63, 64]. Inspired by the framework of motivational interviewing [64], the first question “How important is it for you not to drink alcohol? What do you think about that at this very moment?” [63] will be followed by the statement “I will do everything to get my alcohol problem under control.” [64]. Third, general self-efficacy will be assessed with one question: “How confident are you that you will be completely abstinent in one year from now?” [41].

A broader concept of alcohol-specific self-efficacy will be measured with the *Alcohol Abstinence Self-Efficacy Scale* (AASE-G [65]), which assesses the patients’ expectations concerning their ability to remain abstinent from alcohol in specific high-risk situations.

Positive and negative alcohol outcome expectancies are quantified with the *Comprehensive Alcohol Expectancy Scale* (CAEQ [66, 67]). A reduced version [67] will be used to assess five dimensions of alcohol expectancies: social assertiveness and positive affect; tension reduction; cognitive impairment and physical discomfort; aggression; and sexual enhancement.

As has been done before [57, 58], *Drinking Goals* will be assessed by asking the patients whether their personal drinking goal is (1) total abstinence and hence no future alcohol use, (2) abstinence with occasional lapses, or (3) controlled and responsible drinking.

Finally, with a self-created *Discharge Questionnaire,* all patients will be asked about occurring relapses during their treatment. Participants will be informed that this information is confidential and will not be shared with the staff of the relevant hospital.

#### Psychopathology

General psychopathology will be assessed with the *Brief Symptom Check List,* (BSCL, formerly BSI; [51, 52]), which comprises of nine primary symptom dimensions (e.g., depression, anxiety, hostility) and three global indices (e.g., global severity index).

Apart from this general measure, several screenings for specific psychopathological syndromes which are often comorbid with AUD will be implemented: the intensity of anxiety symptoms will be assessed with the *Beck Anxiety Inventory* (BAI [68, 69]), and for qualification of the severity of depressive symptoms, the *Beck Depression Inventory* (BDI-II [70, 71]) will be administered. The *ADHD Self Report Scale* (ASRS-V1.1 [72, 73]) assesses symptoms of Attention Deficit and Hyperactivity Disorder (ADHD). The *PTSD Screening Scale* (PSS; [74, 75]) qualifies symptoms of posttraumatic stress disorder (PTSD).

Additionally, stress (due to loss or experience of negative events) and coping will be assessed with the *Stress and Coping Inventory* (SCI [76]). Subjectively perceived quality of life will be measured with three subscales (global scale, physical and psychological health) from the short version of the *World Health Organization Quality of Life* questionnaire (WHOQOL-BREF [77, 78]).

